## Abstract

**Background:**

Despite strong and growing interest in ending the ongoing opioid health crisis, there has been limited success in reducing the prevalence of opioid addiction and the number of deaths associated with opioid overdoses. Further, 1 explanation for this is that existing interventions target those who are opiate-dependent but do not prevent opioid-naïve patients from becoming addicted.

**Objective:**

Leveraging behavioral economics at the patient level could help patients successfully use, discontinue, and dispose of their opioid medications in an acute pain setting. The primary goal of this project is to evaluate the effect of the 3 versions of the Opioid Management for You (OPY) tool on measures of opioid use relative to the standard of care by leveraging a pragmatic randomized controlled trial (RCT).

**Methods:**

A team of researchers from the Center for Learning Health System Sciences (CLHSS) at the University of Minnesota partnered with M Health Fairview to design, build, and test the 3 versions of the OPY tool: social influence, precommitment, and testimonial version. The tool is being built using the Epic Care Companion (Epic Inc) platform and interacts with the patient through their existing MyChart (Epic Systems Corporation) personal health record account, and Epic patient portal, accessed through a phone app or the MyChart website. We have demonstrated feasibility with pilot data of the social influence version of the OPY app by targeting our pilot to a specific cohort of patients undergoing upper-extremity procedures. This study will use a group sequential RCT design to test the impact of this important health system initiative. Patients who meet OPY inclusion criteria will be stratified into low, intermediate, and high risk of opiate use based on their type of surgery.

**Results:**

This study is being funded and supported by the CLHSS Rapid Prospective Evaluation and Digital Technology Innovation Programs, and M Health Fairview. Support and coordination provided by CLHSS include the structure of engagement, survey development, data collection, statistical analysis, and dissemination. The project was initially started in August 2022. The pilot was launched in February 2023 and is still running, with the data last counted in August 2023. The actual RCT is planned to start by early 2024.

**Conclusions:**

Through this RCT, we will test our hypothesis that patient opioid use and diverted prescription opioid availability can both be improved by information delivery applied through a behavioral economics lens via sending nudges directly to the opioid users through their personal health record.

**Trial Registration:**

ClinicalTrials.gov NCT06124079; https://clinicaltrials.gov/study/NCT06124079

**International Registered Report Identifier (IRRID):**

PRR1-10.2196/52882

## Introduction

Opioid-related overdose and death rates continue to soar in all age groups [1-3]. Today, it is the leading cause of unintentional, injury-related death in the United States [4]. As of 2020, prescription opioid-related deaths totaled more than 16,000 [5]. Even in 2021, despite opiate prescribing reaching a low point, opiate deaths continue to rise [6]. Further, 1 hypothesis to explain this is that existing interventions target those who are opiate-dependent but do not prevent opioid-naïve patients from becoming addicted [7-9]. Once a patient acquires and fills a prescription, they are free to use it however they choose. The continued skyrocketing trajectory of opioid deaths as well as the persistent conundrum of opioid use demonstrates the insufficiency of exclusively relying on prescriber-directed strategies. This highlights the critical need to directly empower individual patients to responsibly manage their use, weaning, discontinuation, and disposal of opioid medications.

Continuous perioperative interventions centered on opioid management and coming from many different angles could contribute to a solution. Evidence has shown that less than 10% of unused opioids are properly disposed of after surgery, suggesting that excess opioids remaining in the home after surgery is a widespread but targetable problem [10]. Diversion of opioids, which is defined as illegal distribution or abuse of opioids for purposes not intended by the prescriber, could be intentional (for example, sharing or selling of medications) or unintentional (for example, theft or ingestion by a child).

Behavioral economics is a field of study within human decision-making where the goal is to predictably influence human behavior and encourage people to do something without forcing, coercing, or penalizing them [11,12]. Several behavioral economics interventions have been leveraged to influence human behaviors but do not guarantee an improvement in the target population’s target behavior. Nudging is a way to manipulate people’s choices to lead them to make specific decisions. Nudging has previously been used to influence smoking, alcohol consumption, diet, and physical activity to improve population health and reduce health inequalities [13]. More recently, nudging has been used to improve medication compliance among patients with various medical conditions, for example, cardiac [14], kidney transplant recipients [15], patients with diabetes [16], HIV [17], and mental illness [18]. Behavioral economics also offers an opportunity to help individuals make choices consistent with responsibly using and disposing of their opioid medications [19].

The primary goal of this project is to evaluate the effect of the 3 versions of the Opioid Management for You (OPY) tool described in the methods section on measures of opioid use relative to the standard of care (SOC) leveraging a pragmatic randomized controlled trial (RCT). We hypothesize that appropriate patient opioid use and diverted prescription opioid availability can both be improved by information delivery applied through a behavioral economics lens via sending nudges directly to the opioid users, that is, patients. We anticipate not only better management of opioid use and its safe disposal but also expect to obtain a better understanding of the unresolved questions regarding how pain medication is used in acute perioperative settings. In the future, we could further optimize the OPY tool, integrating artificial intelligence and other machine learning models for a more enhanced patient experience.

## Methods

### OPY Tool

#### Overview

A team of researchers from the Center for Learning Health System Sciences (CLHSS) at the University of Minnesota partnered with M Health Fairview (MHFV) to design, build, and test the 3 versions of the OPY tool. Based on a literature review of current popular nudging theories implemented in various delivery modes, we incorporated 3 nudging tactics into the workflow of Care Companion to improve patient self-management, medication adherence, and overall health. Tactics were based on the following behavioral economic principles: social influence, precommitment, and testimonial version. Other forms of interventions, including reminders, feedback, and loss-framing, will also be partially incorporated as a component of the design but will not be considered as major guidelines.

The tool is being built using the Epic Care Companion platform and interacts with the patient through their existing MyChart personal health record account and Epic patient portal, accessed through their phone app or the MyChart website. As patients communicate their pill usage, pain scores, or other concerns, the intervention will communicate timely and relevant information regarding opioid use and addiction while also offering encouraging feedback to help patients successfully wean and safely dispose of their opioids. OPY saves the data that a patient enters and based on their responses, the care team is alerted to important issues through an in-basket message system. The alerts or flags are selected and color-coded based on the urgency of action required after discussion with the patient education specialist team.

Each of the 3 OPY versions will deliver the same instructions and information about pain management recommendations and collect the same information about patient pain experience and side effects; however, the behavioral economics techniques used to influence weaning and disposal are different across the 3 versions. The 3 versions will correspond to different treatment arms of the RCT.

#### Version 1, Social Influence and Commitment

Social influence refers to how individuals change their ideas and behaviors to meet the needs in a social environment [20]. Studies have found that social influence has proved effective for physical activity promotion when applied to mobile apps and is also promising in helping manage chronic diseases, including diabetes.

Patients are provided with text that communicates a social norm or expresses an expectation to the patient meant to decrease the average time it takes for patients to begin weaning. Textbox 1 provides an example of social influence text shown to patients.

Example of social influence text shown to patients.Opioid overdoses are at an all-time high. You can help us end this opioid epidemic! When you're ready, we'll help you wean as quickly as possible – and then get rid of your leftover medicine safely.

#### Version 2, Precommitment

Precommitment refers to a commitment we make in advance to ensure our future actions align with our current preferences and eventually reach the goal we set for ourselves [21]. Studies have shown that precommitment effectively ameliorates self-control problems by encouraging healthy diets, less smoking, and reducing temporary drinking. Being cost-effective in many cases [22], precommitment could have positive implications for chronic disease control and prevention [23].

Patients are given the same suggestions as in other versions but are asked to check a box next to the suggestions they are planning to try. Textbox 2 provides an example of precommitment options provided to patients.

Example of precommitment options given to patients.
**Let's try to reduce your opioid pain medicine. Set a goal to use one of the options below — and be sure to tell a friend or family member about your goal.**
Try taking a dose every X+2 hours (instead of X hours).For every other dose, take just half the dose.Try skipping a dose.

#### Version 3, Testimonial

Emerging evidence suggests that storytelling, or narrative communication, influences listeners by actively engaging them in a story, causing them to identify themselves with the storyteller and picture themselves taking part in the action. This approach of leveraging testimonials offers a unique opportunity to promote evidence-based choices in a culturally appropriate context. Stories and storytelling have been previously used as mechanisms to improve patient medication compliance for both hypertension [24] and diabetes [25], as well as improve other health education and literacy programs.

In this approach, instead of text-based nudges or setting goals, the patient receives short videos communicating risks and benefits through narrative storytelling. The videos use voice actors to depict patients who have experienced complications related to opioid use after surgery. A video clip of a person is presented to represent the patient sharing their personal story. Textbox 3 provides an example of testimonial audio presented to patients.

To ensure that videos and their content meet the current in-place requirements of the organization, we worked closely with the patient education team and followed their requirements. We also made sure that the videos were relatable to patients from diverse demographic backgrounds (ie, race, ethnicity, gender, and age) after judicious selection of individual stock video clips from University of Minnesota stock image resources [26] and collecting voice-over audio recordings from our team members who volunteered to read and record the scripts. We will collaborate with the IT team at our implementation sites to create reports on when each patient watched the video and if they watched the full video or left without finishing it. If patients do not complete the video, the task will be flagged to ensure the patient can see and come back later to finish watching the given video.

Example of testimonial audio presented to patients.After having my appendix removed, I took opioids to help with the pain. But, even on the Vicodin my doctor prescribed, I didn't feel great. When my doctor suggested that I start reducing how much I was taking, I didn't want to do that. I wasn't feeling totally better yet. When day 5 came and I hadn't reduced the number of pain pills, I had another problem: constipation. Turns out the pain of going to the bathroom was much worse than the actual pain resulting from surgery. After taking stool softeners along with gradually reducing the dose, I started feeling better in a week. I wish I had started weaning sooner.

#### OPY Functional Description

OPY appears as a task within MyChart. The first OPY tasks present welcome text for first-time users that describes what OPY is and how to use it. OPY asks users if they want to use OPY or if they want to opt out. OPY tasks and questions will not appear again for people who opt out. OPY then asks patients about their comfort with filling out medical forms and their safety taking ibuprofen or acetaminophen. The medical form information is used to stratify results in our analysis, and the medication question is used to customize pain management suggestions on subsequent days. OPY users must complete these questions before receiving other content from OPY. OPY presents customized messages and questions based on the duration of time since surgery and the responses of the patient. On day 0 (the day of surgery), only the questions described will be asked. OPY patients will not know which version of OPY they are using, or that other versions exist. After day 0, a patient who has opted in will receive several questions every day offered in this order: OPY asks about side effects with prespecified suggestions for what to do for each side effect that they check, pain levels, and the number and frequency of pills they took in the last 24 hours (Figure 1).

Responses are then customized based on the number of days since surgery, patient pain level, and patient pill intake. Depending on their responses, patients receive some combination of pain management advice, including recommendations to take ibuprofen or acetaminophen if able and other standard nonmedication strategies, weaning advice on when and how to start, and disposal advice, including instructions on how and where to dispose of opioids.

At the end of the pathway, all patients will receive a patient satisfaction survey which is standard and exists as an important element of all Epic Care Companion protocols.

Once OPY patients indicate they are taking 0 opioids per day, they will be asked at most 5 times to dispose of the opioids over a span of at most 25 days. OPY will become inactive after 15 consecutive days of no response counted either from day 0 or the last response submitted. Figure 2 summarizes the flow of events that a patient encounters once they are enrolled in the OPY journey.

As per randomization strategy, patients would be assigned one of the following paths: null pathway, pathway 1, pathway 2, or pathway 3. The details are explained in Figure 3.

**Figure 1 figure1:**
[figure not shown]
Epic Systems Corporation 2024 screenshots of OPY screen displaying questions and their responses for (A) social influence and (B) precommitment. OPY: Opioid Management for You.

**Figure 2 figure2:**
[figure not shown]
Flow of events once patients are enrolled in OPY. AVS is given to patients after medical appointments to summarize their health and guide future care. OPY: Opioid Management for You.

**Figure 3 figure3:**
[figure not shown]
Randomization strategy. Standard care: null pathway; pathway 1: social influence; pathway 2: precommitment; and pathway 3: testimonial. First question patients receive: welcome to the Opioid Program for You! (OPY), Your care team has enrolled you in a digital opioid management program, “OPY,” … Do you want to take part in OPY? Click Yes to continue. Click No to stop getting these messages (yes or no). The number of available OPY versions will change over time, which will change the randomization ratio (eg, 1 version available=1:1, standard care versus standard care + pathway 1; 2 versions available=1:1:1, standard care versus standard care + pathway 1 versus standard care + pathway 2). We will leverage an existing random number generator that is embedded within the NAÏVE tool platform which will in turn assign a designated OPY pathway based on the ratio prescription from the statistical team. Rx: doctor’s prescription.

### Preliminary Data From the Pilot

We have demonstrated feasibility with pilot data of the OPY app (Pathway 1) by targeting our pilot to a specific cohort of patients undergoing upper-extremity procedures. About 13% of opioid-naïve patients continue to fill opioid prescriptions 90 days after hand surgery, signaling that this patient population could benefit from tools to help manage opioid use [27]. Another population that we included in the pilot is breast surgery patients, specifically opioid-naïve patients undergoing lumpectomy, mastectomy, mastopexy, and reduction mammaplasty. In total, 10% of opioid-naïve women continued to fill their prescriptions 3 months after breast reconstruction surgery [28]. Over the initial 15 weeks from August of the pilot, 100 patients were eligible to use OPY. In total, 47 (44%) of eligible patients did not interact with OPY to either opt-in or opt-out. Further, 26 (26%) patients opted out of participating in OPY and 27 (27%) opted into using OPY. There is also evidence of persistent engagement with the OPY app, with 24 (65%) of opted-in patients using the tool at least once in the first 4 days after surgery, and 16 (33%) of opted-in patients using the tool at least twice in the first 4 days after surgery as of August 10, 2023.

The preliminary data from the pilot indicates low patient engagement in continuous use. To identify the exact reason why patients were not using the OPY tool as we expected them to, we reached out to patients, their families, and even perioperative nurses. We found a few reasons, the most prominent one being introducing patients and their families to a new tool such as OPY on the day of surgery which was not considered as an effective approach. Patients are already stressed, under the influence of anesthesia, and are overwhelmed with new information. To ensure that we address those concerns, we came up with certain strategies to improve patient compliance, for example, introducing OPY during preop clinic visits, sending epic care companion messages 3 days before surgery sharing what OPY is all about, and also considering options where a nurse (who normally call on postop day 1 to ask about patient progress or pain) to remind them about OPY tool and its benefits.

### Study Design

This study will use a group-sequential RCT design to test the impact of this important health system initiative. Patients who meet OPY inclusion criteria will be stratified into low, intermediate, and high risk of opiate use based on their type of surgery. We used preliminary data to categorize surgery types according to their risk of opiate use. We ranked surgery types according to their opiate use rates at 14 days and categorized surgery types with use rates belonging to the lower 60 percentile, 60-75 percentile, and upper 25 percentile into low, intermediate, and high-risk opioid use groups (surgical risk groups in Multimedia Appendix 1). We estimate the prevalence of these subgroups to be approximately 49%, 34%, and 17%. Randomization will be stratified by baseline risk group, and, within a group, participants will be randomized equally to the SOC (the control group or nonintervention arm) or SOC plus one of the available OPY versions.

### Participant Characteristics, Sample Size, and Recruitment Strategies

#### Inclusion Criteria

We will enroll opioid-naïve patients, aged 18 years or older, including pregnant women, prisoners, and underserved populations who can read and understand English and are undergoing surgery at the MHFV Clinics and Surgery Center—Maple Grove (Maple Grove) or MHFV Clinics and Surgery Center—Minneapolis. Currently, only outpatient surgeries are performed at MHFV Clinics and Surgery Center—Minneapolis and MHFV Clinics and Surgery Center—Maple Grove. Any patient on active opioid prescription (prescribed between 30 days before surgery and until the day of surgery) who was not previously randomized or exposed to OPY would be included. All patients with cancer would be included.

#### Exclusion Criteria

We will exclude patients aged younger than 18 years; those with chronic opioid use, defined as 3 or more opioid dispensing events in the last 12 months with at least 1 of these events in the last 6 months; patients with any long-acting opioid prescription in the last 6 months; patients with a health proxy (legal guardian) designated in Epic; patients who have opted out of clinical research; and patients with an active palliative care referral.

Children are excluded due to complexities in postoperative care and communication.

#### Sample Size

The study will enroll up to 3500 participants (approximately 1715, 1190, and 595 enrollments to the low, intermediate, and high-risk groups, respectively) in each OPY version.

#### Recruitment

We will recruit patients who are undergoing surgery with participating providers at the 2 predetermined locations, that is, MHFV Clinics and Surgery Center in Minneapolis and the Maple Grove locations. Patients who opt out of clinical research or for whom opt-out status is missing will be excluded. The patient is given a choice to consent or opt out of the OPY journey during their first postoperative interaction with the OPY questionnaire distributed through Epic Care Companion. The final decision to participate or not in the OPY journey would be collected from the patient on the day of the surgery (end of the day) through the OPY questionnaire distributed through Epic Care Companion leveraging MyChart.

### Study Duration and Data Management

We anticipate that the pragmatic trial will be implemented over 24 months. Our trial will continue enrollments until we reach our 3500 patients enrollment goal. We rely entirely on collaboration with MHFV for data collection within the CLHSS and Fairview data specialist teams. This is because these efforts require the creation of new data fields that leverage a learning health system platform. Unless specified, we will use naturally collected NAÏVE data (including OPY usage) to assess process fidelity, patient safety, and impact on outcomes.

This project will use the existing CLHSS or Center for Quality Outcomes, Discovery, and Evaluation database covered by the institutional review board (IRB) under 597 Protocol (STUDY00014481). The research database lives within Fairview IT. At Fairview, IT access is facilitated by Fairview Research. Please see the data governance processes described in IRB 597 Protocol (STUDY00014481) for further details. This study will rely on the surgical data mart for data acquisition outside of (1) the data primarily generated through the patients’ clinical participation in the OPY tool and (2) follow-up surveys.

Data will not be shared publicly. Access is regulated by the CLHSS and Fairview Data stewards. Additional sharing beyond the focus of this study would require additional IRB approval.

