### Efficacy Analysis

The study will enroll up to 3500 participants (approximately 1715, 1190, and 595 enrollments to the low, intermediate, and high-risk groups) in each OPY version. Interim and final analyses efficacy analyses will be conducted every 3 months, separately for each surgery risk group, using an O’Brien-Fleming type error-spending function approach to account for the multiple interim and final analyses. Risk-group-specific group-sequential hypothesis tests will use a 1-sided 5% type I error level, to control the overall type I error for each of the 3 interventions at a 15% type I error level.

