### Power Analysis

Based on our initial estimates of the 14-day opioid use rates (0.03, 0.07, and 0.16) for the SOC in each of the 3 subgroups and an odds-ratio treatment effect of 2.0 (opioid use rates 0.015, 0.037, and 0.087), the group-sequential design has 64%, 82%, and 85% power to detect positive treatment effects in the low, intermediate, and high-risk subgroups.

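### The figure 3500 is the size for each OPY version in one place and the trial's enrolment goal in another; the stated power fits only 3500 per version-versus-SOC comparison

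*Protocol article*

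**What the plan says.** Sample Size sets the target as follows: "enroll up to 3500 participants (approximately 1715, 1190, and 595 enrollments to the low, intermediate, and high-risk groups, respectively) in each OPY version". Efficacy Analysis repeats the same numbers with the same unit. Study Duration and Data Management, the only place that says when enrolment ends, states: "Our trial will continue enrollments until we reach our 3500 patients enrollment goal".

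Power Analysis takes "14-day opioid use rates (0.03, 0.07, and 0.16) for the SOC", assumes "an odds-ratio treatment effect of 2.0 (opioid use rates 0.015, 0.037, and 0.087", and reports that "the group-sequential design has 64%, 82%, and 85% power". Efficacy Analysis adds that "Risk-group-specific group-sequential hypothesis tests will use a 1-sided 5% type I error level", with O'Brien-Fleming type error spending and analyses every 3 months.

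Three OPY versions are planned, each compared with SOC. Study Design specifies equal allocation to SOC and the versions then available. The Figure 3 caption says the number of available versions, and hence the ratio, will change over time: 1:1 with one version, 1:1:1 with two. The article nowhere gives N per arm, N per version-versus-SOC comparison, or a total for the three-version trial.

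**The concern.** One number cannot be both the size for each version and the size of the trial unless only one version is ever tested, and the stated aim is to evaluate three. The sentence in Study Duration and Data Management is operational: a team that follows it closes recruitment at 3500. If more than one version has been opened by then, not every comparison can have the sample size that the power statement needs.

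The planned maximum N also fixes the information fraction for error spending and enters the predicted-power futility rule, so the ambiguity reaches the interim decisions as well as the final analysis.

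**Working it through.** **Inputs**
- Risk-group shares of 49%, 34% and 17% (Study Design): 3500 × 0.49 = 1715, 3500 × 0.34 = 1190, 3500 × 0.17 = 595. These agree with Sample Size.
- SOC rates 0.03, 0.07 and 0.16, and an odds ratio of 2.0 (Power Analysis). Halving the odds exactly gives 0.0152, 0.0363 and 0.0870; the article prints 0.015, 0.037 and 0.087.
- One-sided 5% in each risk group (Efficacy Analysis).
- Number of looks: not stated. 24 months at 3-month intervals gives 8; equal spacing is assumed.

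**Step 1: reproduce the stated power.** Take 3500 as OPY plus SOC for one version, so half of each risk group is in each arm: 857.5, 595 and 297.5. For a fixed-sample Wald test on the log odds ratio,

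SE = √[1/(n·p₀(1−p₀)) + 1/(n·p₁(1−p₁))], power = Φ(ln 2/SE − 1.645).

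- Low: SE = √(0.0401 + 0.0778) = 0.343; 0.693/0.343 = 2.019; Φ(0.374) = 65%.
- Intermediate: SE = √(0.0258 + 0.0481) = 0.272; 0.693/0.272 = 2.550; Φ(0.905) = 82%.
- High: SE = √(0.0250 + 0.0423) = 0.260; ratio 2.671; Φ(1.026) = 85%.

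A simulated group-sequential test followed: pooled z-test, spending function 2[1 − Φ(z₀.₉₇₅/√t)], 8 looks, no futility stop. It gives 65.6%, 82.1% and 85.0%. The stated 64%, 82% and 85% is therefore reproduced within 2 points. With the printed rates in place of exact odds-ratio rates the simulation gives 66.7%, 80.2% and 84.9%, so the low-risk figure is then nearly 3 points off, but this is still much the closest reading.

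**Step 2: the other readings.** Only n per arm changes, so the ratio ln 2/SE scales with √n. For four equal arms, n is halved. In the low-risk group, 2.019/√2 = 1.428 and Φ(1.428 − 1.645) = 41%.

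| Reading of 3500 | n per arm (low / int. / high) | Fixed-sample Wald, % | 8-look simulation, % |
|---|---|---|---|
| One version plus its SOC | 857.5 / 595 / 297.5 | 65 / 82 / 85 | 65.6 / 82.1 / 85.0 |
| Each OPY arm, equal SOC arm | 1715 / 1190 / 595 | 89 / 98 / 98 | 89.2 / 97.8 / 98.5 |
| Whole trial, two versions, 1:1:1 | 572 / 397 / 198 | 50 / 67 / 70 | 49.8 / 67.2 / 70.5 |
| Whole trial, three versions, 1:1:1:1 | 429 / 298 / 149 | 41 / 56 / 60 | 41.3 / 55.6 / 59.8 |

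The high-risk figure in the last row varied between 59% and 60% over repeated simulations. With 4 looks that row becomes 41.6%, 56.5% and 60.2%, so the inferred number of looks matters little.

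**Step 3: futility.** Applying a stop below 15% predicted power (8 looks, printed rates) gives 54%, 67% and 73% for the first row, 80%, 90% and 93% for the second, and 35%, 44% and 48% for the last. None of these matches the stated power, so the match in Step 1 is for power before futility stopping.

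**Step 4: implied totals if 3500 is per comparison.** Three versions with one fully shared concurrent SOC arm: 4 × 1750 = 7000. Two versions: 3 × 1750 = 5250. Three versions run one after another, each with its own controls: 3 × 3500 = 10,500. One version only: 3500, and the two statements coincide.

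**Step 5: staggered roll-out, as an illustration.** Assume 3500 in total, with equal thirds recruited while one, two and then three versions are open, and comparison with concurrent SOC only. The share of the 3500 in each arm of a comparison is then
- version 1: (1/3)(1/2 + 1/3 + 1/4) = 0.361
- version 2: (1/3)(1/3 + 1/4) = 0.194
- version 3: (1/3)(1/4) = 0.083

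Fixed-sample Wald power is about 53/70/73% for version 1, 35/48/51% for version 2 and 21/27/29% for version 3.

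**The case against.** The strongest reply is that the sentence on the 3500 goal is shorthand. It sits in a section on duration and data handling, it refers to a goal already defined, and the only definition in the article is per version. Read that way, Sample Size, Efficacy Analysis and Power Analysis agree and no power is lost. This may well be what was intended. It does not settle the matter, because that sentence is the only statement of when enrolment ends and its subject is the trial. The per-version wording is itself loose: taken as arm size it gives about 89%, 98% and 98%, which is not the stated power either.

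A second reply stands in full. A reader might infer that the trial will have 41%, 56% and 59% power. The documents do not support that as a single result, since it requires all three versions to be open throughout at 1:1:1:1, and the Figure 3 caption says the number of versions and the ratio will change. A reader might also infer that the need is at least double the 3500 whatever happens. That holds for three versions; for two with a shared SOC arm the factor is 1.5, and for one it is 1. Nor would lower power make a null result uninterpretable: it widens the confidence interval, which can still be read.

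Finally, neither the sums nor the stated power is a miscalculation. The power is right for one unit of 3500; the fault is that the article does not keep to that unit.

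**Conclusion.** The point holds as an inconsistency in the unit of 3500 and should be corrected. The stated power is tied to 1750 per arm in each version-versus-SOC comparison (about 858, 595 and 298 per arm by risk group). A trial-wide limit of 3500 cannot supply that to more than one version. With two or three concurrent versions the shortfall from the stated power is roughly 14 to 15 points (64 − 50, 82 − 67, 85 − 70) or 23 to 26 points (64 − 41, 82 − 56, 85 − 59). Under a staggered start the loss is uneven and falls most heavily on the latest version.

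These figures rest on exact odds-ratio rates, eight equally spaced looks (inferred), no futility stopping and, for the concurrent scenarios, equal allocation throughout. Which reading the sponsor intends cannot be determined from the article.

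**What to change.** State three numbers together: N per arm, N per version-versus-SOC comparison, and N for the trial, each by risk group where relevant.

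- If 3500 is per comparison, say so (1750 per arm) in Sample Size and Efficacy Analysis. In Study Duration and Data Management, replace the trial-wide 3500 with the implied total: 7000 for three versions with a fully shared concurrent SOC arm, up to 10,500 if they run one after another. This costs only wording if that was always the plan. The 24-month duration should then be checked against the larger total, as the article gives no expected recruitment rate for the trial.
- If 3500 is the true cap for the trial, keep it and replace 64%, 82% and 85% with power for each version, recomputed under the planned roll-out and allocation. This needs no extra patients, only the recalculation. The concurrent-arm figures above should not be copied in as the restated power unless that is the planned allocation.

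In either case, give the number and timing of looks and say whether the quoted power is before or after futility stopping.
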